## Abstract

**Background:**

Endometriosis-related pain encompassing dysmenorrhea, dyspareunia, and chronic pelvic pain, reduces the quality of life in premenopausal women. Although treatment options for endometriosis alleviate this pain, approximately one-third of women still experience pain even after receiving treatment, indicating the need for novel approaches to pain relief in those women. The Angel Touch device (AT-04) is a portable magnetic fields irradiation device that incorporates a combination of mixed alternative magnetic fields at 2 kHz and 83.3 MHz. A phase III trial confirmed the efficacy and safety of AT-02, a prototype of AT-04, for pain relief in patients with fibromyalgia.

**Methods:**

This is a phase III, multicenter, prospective, randomized, sham device-controlled, double-blind, parallel study. The participants will be premenopausal women aged > 18 years who have endometriosis-related pain with at least moderate severity. Considering dropouts, 50 participants have been deemed appropriate. Eligible women will be centrally registered, and the data center will randomly allocate them in a 1:1 ratio to the intervention and control groups. Women in the intervention group will receive electromagnetic wave irradiation generated by AT-04 and those who in the control group will wear a sham device for 16 weeks, and both groups will wear AT-04 for another 4 weeks. The primary outcome measure is the change in the Numeric Rating Scale score at 16 weeks compared with the baseline. Secondary outcome measures are efficacy for pelvic pain including dysmenorrhea and non-menstrual pain, and chronic pelvic pain not related to menstruation, dysmenorrhea, and dyspareunia, and improvement of quality of life during the study period. Safety will be evaluated by device defects and the frequency of adverse events. The study protocol has been approved by the Clinical Study Review Board of Chiba University Hospital, Chiba, Japan, and will be conducted in accordance with the principles of the Declaration of Helsinki and the Japanese Clinical Trials Act and relevant notifications.

**Discussion:**

This study aims to develop a novel method of managing endometriosis-related pain. The AT-04 is an ultralow-invasive device that can be used without inhibiting ovulation, suggesting potential benefits to women of reproductive-age.

*Trial registration number* Japan Registry of Clinical Trials (jRCTs032230278).

**Supplementary Information:**

The online version contains supplementary material available at 10.1186/s12978-024-01739-8.

## Background

Endometriosis is a progressive, chronic inflammatory disorder that affects approximately 10% of women of reproductive age. It generally develops in late adolescence to early adulthood, and the associated symptoms often appear in the late twenties and early thirties [1]. Women with endometriosis experience endometriosis-related pain, encompassing dysmenorrhea, dyspareunia, and chronic pelvic pain, which reduces their quality of life and decreases labor productivity. Although endometriosis-related infertility and ovarian malignant tumors arising from ovarian endometriotic cysts are also important, controlling endometriosis-related pain is of utmost importance when treating endometriosis [2]. Current standard treatments for endometriosis include progestin-based hormonal treatments, such as combined oral contraceptive (OC) pills, gonadotropin-releasing hormone (GnRH) analogs, and laparoscopic surgeries [3]. Analgesics and traditional Chinese medicines are also prescribed to relieve endometriosis-related pain; however, these treatments may be completely ineffective or insufficient in some women, even if appropriate treatments are administered [4]. Additionally, endometriosis-related pain often persists even after laparoscopic excision of endometriotic lesions, indicating that controlling disease progression does not necessarily lead to pain relief. Worsening pain symptoms can trigger anxiety and depression, leading to a further decrease in quality of life and labor productivity [5].

Endometriosis severity does not necessarily correlate with pain intensity, indicating that pain development in patients with endometriosis involves complex mechanisms. Hence, in addition to lowering the pain threshold due to persistent chronic pelvic pain, chronic inflammation, peripheral and central pain generators, endocrine changes, and structural alterations in the peripheral and central nervous systems are also associated with pain [6]. Upregulation of vascular endothelial factors and nerve growth factors as well as proliferation of sensory nerves in local endometriotic lesions may also be associated with pain [7]. Furthermore, the presence of treatment-resistant endometriosis-related pain may indicate the progression of local endometriotic lesions.

The Angel Touch device (AT-04, ait^®^, developed by Peace of Mind Co., Ltd., Kumamoto, Japan) is a portable magnetic fields irradiation device that incorporates a combination of mixed alternative magnetic fields at 2 kHz and 83.3 MHz (magnetic field energy is approximately one-third of the Earth’s magnetic field). Local pain relief may be achieved by carefully using this device on the affected area. Animal experimental data has revealed that the pain control mechanism of this device involves the regulation of nerve growth factors, local inhibition of inflammatory cytokines, and activation of the descending inhibitory system [8]. These are the possible mechanisms that control endometriosis-related pain. A phase III clinical trial confirmed the efficacy and safety of AT-02, a prototype of AT-04, for pain relief in patients with fibromyalgia [9]. Moreover, a pilot study using AT-04 for pain relief from dysmenorrhea in five women with endometriosis conducted in our laboratory revealed that dysmenorrhea significantly improved without any adverse events, and the size of the endometriotic cysts significantly decreased (data not shown). These results prompted the need for large-scale validation studies to identify the efficacy and safety of AT-04 for pain relief in women with endometriosis.

## Methods

### Aim

The aim of this study is to explore the efficacy and safety of AT-04 in women with endometriosis-related pain.

### Design and setting

This is a phase III, sham-controlled, double-blind, parallel-group study. This study will be conducted in the Chiba University Hospital and its affiliated facilities, The University of Tokyo Hospital, University of Yamanashi Hospital, Fukuoka University, KASHIWAZAKI OB/GYN CLINIC, Iryohojinshadan Seijunkai Juno Vesta Clinic Hatta, TSUBAKI Women’s Clinic, and Yokosuka Haruko Lady’s Clinic. Details of the participating research facilities are provided in Additional file 1.

### Study participants

#### Inclusion criteria

Participants must fulfil the following inclusion criteria:Premenopausal women aged ≥ 18 years at the time of obtaining consentPatients clinically diagnosed with endometriosis meeting one of the following criteria (additional diagnosis required if the disease recurs after surgery):laparoscopy or laparotomy performed within 5 years of the start of treatmentmagnetic resonance imaging or ultrasonography (transvaginal, transabdominal, or transrectal) performed within 1 year prior to the start of treatmentpelvic and rectal examination performed prior to the start of treatmentPatients with dysmenorrhea or pelvic pain believed to be caused by endometriosis, with at least one assessed by the principal investigator to be moderate or higher on the Biberoglu and Behrman (B&B) rating scale before the start of treatment [10]Patients with an average Numeric Rating Scale (NRS) score ≥ 4 for endometriosis-related pain within 28 days before obtaining consent [10]Patients who have not initiated any new treatment for endometriosis or made changes to their existing treatment (including prescription details, dosage, and administration) within 28 days before obtaining consentPatients who, based on the assessment of the principal investigator, show no evidence of acute endometriosis deterioration within 28 days before obtaining consent.Patients who provide written consent to participate in the study.

#### Exclusion criteria

Patients meeting the following criteria will be excluded:Use of the following drugs within 8 weeks prior to obtaining consent: clinical trial or investigational drugs, GnRH analogs, danazol and aromatase inhibitors, and selective estrogen receptor modulatorsPrevious use of alternating magnetic field therapy devices, including the study devicesPatients who routinely use non-steroidal anti-inflammatory drugs (NSAIDs)Patients with ovarian endometriotic cysts > 10 cm in diameter and aged > 40 yearsHistory of bilateral oophorectomySignificant or unexplained irregular uterine bleeding determined by the principal investigatorPatients with uterine fibroids who may require new treatment during the study period in the opinion of the principal investigatorIrritable bowel syndrome and/or lower abdominal pain due to severe interstitial cystsPatients with a history of, or complications of, severe hepatic disorder, jaundice, renal disorder, cardiovascular, endocrine system, metabolic, pulmonary, gastrointestinal, neurological, or urological diseases, immune disorders, psychiatric diseases (especially depression-like symptoms), and suicide attempts due to such disordersPatients using life-supporting medical electrical equipment such as artificial heart lungs and pacemakersPatients using medical electrical equipment, such as electrocardiographsPatients participating in clinical trials or clinical studies on other drugs or medical devicesPatients requiring hospitalization for treatment

### Participant screening

Consent will be obtained from eligible participants 28–35 days before randomization. The examination items at screening will encompass the following items:Participant characteristics at the baseline, including the date of consent, patient identification code, age, height (cm), weight (kg), body mass index (BMI), medical history, comorbidities, prior treatments, and physical findings, including major symptoms of endometriosis, gravidity, and parityVital signs, including systolic and diastolic blood pressure and body temperatureEvaluation of subjective and objective pain symptomsDetermination of the average NRS score for the 4 weeks preceding the visitEvaluation of the B&B scoreUltrasound examination to identify ovarian endometriotic cysts and other endometriotic lesions. For assessment of ovarian endometriotic cysts, the maximum diameter of each cyst and their perpendicular diameter will be measured, and the calculated volume (cm^3^) will be recorded.Monitoring the occurrence of adverse eventsDocumentation of concomitant medications and therapies.

### Discontinuation criteria

The study will be terminated if any of the following criteria are met during the study period:Occurrence of unexpected severe illnesses or conditions, including physical disability or death, events that may lead to physical disability or death, hospitalization or extension of hospital stay, and congenital disorders or abnormalities in the next generationFrequent occurrence of predictable severe conditions that significantly exceed expectationsSerious adverse events for which a causal relationship cannot be excludedReports indicating significant changes in the incidence, frequency, and conditions of disease occurrenceReports indicating the potential occurrence of cancer, other serious diseases, disabilities, or deathInformation suggesting a lack of efficacy in the trialInformation on measures implemented to prevent manufacturing, importation, or sale, as well as recall, disposal, or other actions to prevent the occurrence or spread of health and hygiene hazards for commercial products having the same effect as the tested devices.

### Study device

The AT-04 is a minimally invasive device comprising a controller and a dual-coil emitter assembly powered by a 3.7-V battery (Fig. 1a). The dual emitter simultaneously generates alternating magnetic fields. Detailed instructions, in Japanese, for using the device are provided in the Additional file. Briefly, participants are instructed to attach two pads to the left and right sides of the lower abdomen and then press the start button to generate local electromagnetic waves (Fig. 1b). The device automatically stops after 30 min. If participants experience pain in areas other than those mentioned above, they can attach the remaining two pads to the affected area(s). The test and sham devices will be provided free of charge by Peace Mind Co. Ltd., Kumamoto, Japan.

**Fig. 1 Fig1:**
[figure not shown]
Study device and location for applying pads. **a** Actual photo of the AT-04. The appearance of the test device (AT-04) and the sham device (S-02) is identical, and it is impossible to distinguish the two based on their external features. **b** Location for applying pads. Participants will attach the pads themselves to both sides of their lower abdomens. The grey circle indicates the basic location for applying the pads

### Interventions

The study design is shown in Fig. 2. After obtaining consent, eligibility for this study will be confirmed through screening tests. Central enrolment and randomized assignment will be conducted at the data center using a 1:1 ratio to minimize bias. The actual treatment group will use the AT-04 and the control group will use the S-02, a sham device, for 16 weeks. At the 16-week visit, participants will be asked to bring their device for replacement with a new device (all actual devices). To ensure blinding after replacement with the actual device at week 16, participants will be informed, at the time of obtaining their consent to participate, that the feeling of use may vary depending on the device under study. The pads will be applied to at least two sites on the lower abdomen, including the uterine and ovarian areas; if there are other painful areas, two additional pads (a maximum of four sites) will be applied to those areas.

**Fig. 2 Fig2:**
[figure not shown]
Overview of the study design. After providing consent, eligible women will be randomly assigned to the treatment group, utilizing AT-04, or the control group, utilizing S-02. Participants will use these devices for 16 weeks (double-blind period), after which they will use AT-04 for an additional 4 weeks (actual device usage period)

### Outcome measures

#### Primary outcome

The primary outcome of this study is the change in the NRS score for endometriosis-related pain collected at each visit and at the end of the double-blind period (after 16 weeks) compared with the baseline score at the start of treatment.

#### Secondary outcomes

The secondary outcomes of this study are summarized in Table 1. Measurements will be conducted at the baseline and at 4, 6, 12, 16, and 20 weeks after treatment initiation. Longitudinal pain during the study period will be recorded using electronic patient-reported outcomes (ePRO). The B&B scale, a specialized scoring system for evaluating endometriosis-related pain, will be employed. It consists of a rating based on the patient’s self-assessment of pelvic pain, dysmenorrhea, and dyspareunia (Bourdel et al. 2014). The quality of life of the participants will be evaluated using the Endometriosis Health Profile-30 (EHP-30) and the EuroQol 5-Dimension (EQ-5D) Health-Related Quality of Life (HRQoL) Questionnaire.

**Table 1 Tab1:** Secondary outcomes in this study

Outcomes		Evaluation tools	Time points
Efficacy for pain	Pelvic pain	NRS score	Comparison baseline* with 4, 8, 12, and 20 weeks after treatment initiation
	Pain during menstruation#	NRS score by ePRO^$^	From treatment initiation to end of treatment
	Pain other than menstruation	NRS score by ePRO^$^	From treatment initiation to end of treatment
	Chronic pelvic pain not related to menstruation, dysmenorrhea, and dyspareunia	Biberoglu & Behrman (B&B) scale	Comparison baseline* with 4,8,12, and 20 weeks after treatment initiation
Quality of life		Endometriosis Health Profile-30 (EHP-30) score	Comparison baseline* with 4, 8, 12, and 20 weeks after treatment initiation
		Health-related quality of life (EQ-5D)	Comparison baseline* with 4, 8, 12, and 20 weeks after treatment initiation
Efficacy for endometriosis lesions	Size of ovarian endometriotic cysts	Transvaginal ultrasound	Comparison baseline* with 16 weeks after treatment initiation**
Safety of the device	The frequency and proportion of malfunctions and adverse events in the test device		

*Baseline was defined as a point before treatment initiation

^#^Pain during menstruation including menstrual pain and other pelvic pain

^$^eRPO: Electronic Patient-Reported Outcomes; NRS: Numeric Rating Scale

**Time at the end of the treatment period

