#### Observation, examination, and evaluation items at each visit (Table 2)

**Table 2 Tab2:**
[figure not shown]

[figure not shown]
Study schedule for observation, inspection, and evaluation

● Represents the examination and assessment items to be performed at each visit

^#^1: Acceptable range of the required tests at Day 1, as indicated by 〇, are 14 days. Treatment using test device starts at Day 1

^#^2: Consent from the participants must be obtained at least 28 days before the start of the study

^#^3: Participants recall and assess the level of pain experienced over the past 4 weeks at each visit

^#^4: Data collected through the electronic Patient Reported Outcome (ePRO) system will be used for the assessment

^#^5: The participant diary will start recording from the date of consent. Recordings until the day before Day1 will be on paper diary, while from Day1 onwards, record will be collected by ePRO

BMI: body mass index; NRS: Numeric rating Scale; B&B: Biberoglu and Behrman; EHP-30: Endometriosis Health Profile-30; EQ-5D: EuroQol 5-Dimension

Treatment using the test device will commence on Day 1, and the NRS, B&B, EHP-30, and EQ-5D scores will also be collected on Day 1. NRS scores will be assessed by participants recalling their endometriosis-related pelvic pain over the 4 weeks prior to the visit. The following items will be assessed at the visits in weeks 4, 8, 12, 16, and 20 after the initiation of the trial:Height and BMIVital signs, including systolic and diastolic blood pressure and body temperatureSubjective and objective pain symptomsAverage NRS score for the 4 weeks preceding the visitMaximum and average NRS scores during menstruation within the 4 weeks preceding the visitMaximum and average NRS scores for periods other than menstruation within the 4 weeks preceding the visitB&B, EHP-30 score, and EQ-5D scoresUltrasonography to identify ovarian endometriotic cysts and other endometriotic lesions. Ovarian endometriotic cysts will be evaluated using the same measurements as the screening examinationOccurrence of adverse eventsConcomitant medications and therapies.

In the event of discontinuation of the device by a participant, the reasons for discontinuation will be included in addition to the observation items mentioned above.

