### Statistical analysis

The baseline characteristics for participants in each group will be summarized, presenting frequencies and percentages for categorical variables and summary statistics (number of cases, mean, standard deviation, and minimum, median, and maximum values) for continuous variables. For group comparisons, Pearson’s Chi-squared test will be used for categorical variables, Fisher’s exact test will be applied for cells with an expected frequency < 5% and > 20%, and the t-test or Mann–Whitney U test will be used for continuous variables.

A two-tailed 5% significance level will be used. A two-tailed Student’s t-test will assess the primary outcome (null hypothesis: the difference in NRS score change between the treatment and control groups equals zero; alternative hypothesis: the difference in NRS score change between the treatment and control groups is not equal to zero). Rejection of the null hypothesis and adoption of the alternative hypothesis will occur if p < 0.05.

Additionally, an analysis of variance with the allocation factor as a fixed effect will be performed as a sensitivity analysis, and the Wilcoxon rank-sum test will be performed for a non-parametric analysis. The secondary endpoint analysis will be similar to the primary endpoint analysis. For the safety endpoint, frequencies and proportions of the patients with adverse events will be presented for each group. Exact two-sided 95% confidence intervals, assuming a binomial distribution, will be calculated for each group, and Fisher’s exact test will be used to compare groups. All statistical analyses will be performed using SAS version 9.4 or higher (SAS Institute Japan Ltd, Tokyo).

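### Table 1 omits week 16, the end of the double-blind period, from the B&B, EHP-30 and EQ-5D comparisons, and the only later time point it lists, week 20, is not sham-controlled

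*Protocol article*

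**What the plan says.** **Comparison times.** In Table 1 (Secondary outcomes), the rows for pelvic pain NRS, EHP-30 and EQ-5D read "Comparison baseline* with 4, 8, 12, and 20 weeks after treatment initiation". The B&B row lists the same four weeks. Among the rows with fixed comparison visits, only cyst size names week 16: "Comparison baseline* with 16 weeks after treatment initiation".

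**Measurement times.** The paragraph above the table says "Measurements will be conducted at the baseline and at 4, 6, 12, 16, and 20 weeks after treatment initiation". The section on items at each visit says "The following items will be assessed at the visits in weeks 4, 8, 12, 16, and 20 after the initiation of the trial", and its list includes B&B, EHP-30 and EQ-5D.

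**Design.** The Fig. 2 legend says "Participants will use these devices for 16 weeks (double-blind period), after which they will use AT-04 for an additional 4 weeks". The Interventions section confirms that devices are exchanged at the week-16 visit and that all replacements are active.

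**Analysis.** The primary outcome is the change in NRS "at the end of the double-blind period (after 16 weeks) compared with the baseline score at the start of treatment", tested between groups with a two-sided Student's t-test at the 5% level. For the rest, the Statistical analysis section says "The secondary endpoint analysis will be similar to the primary endpoint analysis".

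**The concern.** Leaving week 16 out of the pelvic pain NRS row is logical, because week 16 is the primary outcome and is defined elsewhere. That reason does not apply to B&B, EHP-30 and EQ-5D, whose week-16 value is not named as a comparison anywhere. The list may have been carried over from the NRS row; the article gives no reason for dropping the last visit of the randomised comparison while keeping one after it.

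Two things are at stake. First, quality of life and B&B pain could not be set beside the week-16 primary result at the same time point under the published table, and adding week 16 once results are known would invite a charge of selection. Second, if the primary-type analysis is applied at every listed week, the week-20 result would appear in the same series as weeks 4, 8 and 12 although it answers a different question.

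**Working it through.** **1. Time points side by side (B&B, EHP-30, EQ-5D)**

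| Week | Collected (items at each visit) | Compared (Table 1) | AT-04 arm | Control arm | Device versus sham? |
|---|---|---|---|---|---|
| 4 | yes | yes | AT-04 | sham | yes |
| 8 | yes | yes | AT-04 | sham | yes |
| 12 | yes | yes | AT-04 | sham | yes |
| 16 | yes | **no** | AT-04 | sham | yes |
| 20 | yes | yes | AT-04 for 20 weeks | sham for 16 weeks, then AT-04 for 4 | **no** |

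Collected {4, 8, 12, 16, 20} minus compared {4, 8, 12, 20} leaves {16}. The one collected visit that is not compared is the last sham-controlled one. Of the four sham-controlled visits, 3 are listed (3/4 = 75%). The last listed one is at week 12 of 16, so the final 16 − 12 = 4 weeks of sham control (4/16 = 25%) have no comparison for these scales.

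**2. A separate mismatch.** The paragraph above Table 1 has {4, 6, 12, 16, 20}; Table 1 and the visit schedule have week 8 and no week 6. This is clerical, but it concerns the same list of time points.

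**3. The plan's own figure.** The sample size section gives SDs of 1.8 (active) and 0.3 (sham), effect size d = 0.969, two-sided alpha 0.05, power 0.90 and 24 per group.

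- Pooled SD = √[(1.8² + 0.3²)/2] = √1.665 = 1.290, and (1.49 − 0.24)/1.290 = 0.969.
- Normal approximation: n = 2(1.960 + 1.282)²/0.969² = 22.4, so 23 per group.
- Noncentral t: the smallest n with power of at least 0.90 is 24 per group, with power 0.908.

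The stated 24 per group is reproduced from the stated d. Nothing in this point changes it.

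**4. Illustration only: a between-group test at week 20.** The article gives no effect size for B&B, EHP-30 or EQ-5D. Assume that d = 0.969 also applied to them at week 16, with 24 per group, and that a fraction f of the between-arm difference remains at week 20. Power then comes from the noncentral t with 2 × 24 − 2 = 46 degrees of freedom and noncentrality f × 0.969 × √(24/2) = f × 3.357.

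| f | d at week 20 | Power |
|---|---|---|
| 1 (as at week 16) | 0.969 | 0.91 |
| 0.75 | 0.727 | 0.69 |
| 0.50 | 0.485 | 0.38 |
| 0.25 | 0.242 | 0.13 |
| 0 | 0 | 0.05 |

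The documents do not say which f to expect. The table shows only that the week-20 result depends on how quickly the control arm responds to AT-04, as well as on any device effect.

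**The case against.** The strongest reply is that this is a slip in one table of a condensed article. The surrounding text includes week 16 for these scales, the data will be collected, the abstract speaks of quality of life over the study period without selecting weeks, and the full protocol and any SAP are not shown. Most of that stands. It makes the defect an internal inconsistency, not evidence of a deliberate choice. It does not remove it: Table 1 states the comparison times explicitly, and what it states conflicts with the design.

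A reader might also infer more than the documents support:

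- **That these outcomes are tested at week 20 instead of under sham control.** Week 20 is listed alongside weeks 4, 8 and 12, all sham-controlled. It replaces nothing.
- **That a week-20 between-group test is prescribed.** Table 1 speaks only of comparison with baseline. The test follows from the general statement that secondary analyses resemble the primary one, which does not settle how the visit after the switch is handled.
- **That the week-20 difference will be near zero.** This needs an onset within four weeks, which the article does not give. The four-week recall window is stated for pain ratings, not for EHP-30 or EQ-5D.
- **That these scales are the main support for the primary result, or that a null at week 20 would be misread.** No section ranks the secondary outcomes, and the article is open about both arms using AT-04 after week 16.
- **That weeks 16 to 20 are unblinded.** The Interventions section describes a measure to keep blinding after the exchange. The point is that both arms use the same device, not that they know it.

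**Conclusion.** The point holds as an inconsistency in the specified comparisons. For B&B, EHP-30 and EQ-5D, Table 1 omits the end-of-double-blind visit, leaves week 12 as the last sham-controlled comparison, and lists afterwards only a visit at which both arms have used AT-04 for four weeks. A between-group difference at week 20 would contrast 20 weeks with 4 weeks of AT-04. That is a legitimate question, but not device versus sham.

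The size is one of four sham-controlled visits for three instruments. This rests on the stated time points alone. The concern about a week-20 test further assumes that the primary-type analysis is applied at each listed week, and the power figures assume an effect size borrowed from the NRS. Because the primary outcome, its test, data collection and sample size are untouched, this should be fixed but is not critical to the trial's validity.

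**What to change.** 1. In Table 1, add week 16 to the B&B, EHP-30 and EQ-5D rows and label it the end-of-double-blind comparison.
2. State once, for every row that lists week 20, that the results describe the period when both arms use the active device and are not a device-versus-sham test.
3. Reconcile week 6 in the paragraph above Table 1 with week 8 in the table and the visit schedule.

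The cost is wording in the table and its text, carried into the SAP if one exists, and settled before unblinding. No visit, measurement or sample size changes. Ranking week 16 as a key secondary time point, or adding a within-patient analysis of weeks 16 to 20 in the control arm, would be optional; the correction needs neither.
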